***Neurologic evaluation***

**National Institutes of Health Stroke Scale (NIHSS)**

The neurological evaluation will be done at baseline and after 2 months for all patients. In the cross group a 3^rd^ evaluation will be performed after 4 month- after crossing and completing 2 months of HBOT treatment. The clinical severity of the stroke will be assess by trained physician according to the National Institutes of Health Stroke Scale (NIHSS)[^69^](#_ENREF_69)^,^ [^70^](#_ENREF_70).

The NIHSS is attached in appendix 1.

**Activities of daily living (ADL)**

The activities of daily living (ADL) will be evaluated by a questioner that covers the following functions: bathing, dressing, grooming, oral care, toileting, walking, climbing stairs, eating, shopping, cooking, managing medications, using phone, housework, doing laundry, driving and managing finances[^71^](#_ENREF_71). For each criterion the patient had to define whether he/she is independent, needs help, dependent or does not do at all (The range of the total score is from 0 (best) to 51 (worst)).

The ADL is attached in appendix 2.

**Brain functional Imaging SPECT imaging and Analysis**

Single photon emission computed tomography (SPECT) will be conducted before and after HBOT. Subjects will lay supine in a quiet dimly lit room for 20 min prior to injection of the radiopharmaceutical. Apart from administration of the injection by a physician, they will remainalone in the room during this period. Subjects will be asked to remain at rest for 10 min after the injection of the radiopharmaceutical to allow uptake of the radiopharmaceutical in the brain.

An injection of 925-1110 MBq (25-30 mCi) of technetium-99m ethyl cysteinate dimmer (Tc-99m-ECD) will be given into an arm vein through a previously placed intravenous cannula. SPECT imaging of the brain was performed, at 40-60 min post injection, with the subject’s head supported by a headrest, using a dual detector gamma camera (ECAM or Symbia T, Siemens Medical Systems) equipped with high resolution collimators. Data will be acquired in the step-and-shoot mode, using a 360 degree circular orbit, with the detectors of the gamma camera as close as possible to the subject’s head. The camera used for imaging will noted for each subject and the same camera will be used for the follow-up study. Data will be acquired using a 128׳128 image matrix in 3 degree steps of 20 seconds per step. Data will be reconstructed by iterative reconstruction with no filtering. The Chang method (*μ*=0.12/ cm) will be used for attenuation correction.

Intra subject visual analysis will be conducted using a process in which pre and post treatment studies are fused and normalized to pre-treatment whole brain activity.

Visual analysis will be carried out by two nuclear medicine physicians who compared the scans independently and grad them as either: 1=no change, 2=mild change and 3=significant change. Where, no change is assign when no visual difference is noted in the number or size of perfusion deficits, mild change is given when a reduced number of perfusion defects are noted or the size of the perfusion defects is reduced. Significant change should be attributed when a global perfusion increment is observe in addition to diminution of defect numbers or size. Differences in evaluation will be resolve after reviewing the images together. Scan visual interpretation will be carried out while blinded to any laboratory or clinical data.

A comparison of the SPECT results with anatomical imaging (CT or MRI) will be done in order to evaluate the extent of perfusion deficit in relation to the anatomical lesion.

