***Study protocol***

After signing the informed consent, patients were randomized in 1:1 manner into the treated or the control-cross group. After the randomization, patients were invited for baseline evaluation that included full review of their medical status and complete physical examination. All patients had baseline CT scan. After their inclusion patients were randomized to two groups: a treated group and a cross group. All patients had evaluation of their neurologic functions by physical examination, ability to perform activities of daily living, quality of life and brain functional imaging (rCBF-SPECT scan). The patients in the treated group were evaluated twice – at baseline and after 2 months of HBOT treatment. The patients of the cross group were evaluated three times – at baseline, after a 2 month control period of no treatment and after a consequent 2 month period of HBOT treatment. We emphasize that the study was a cross-over trial and patients in the cross group received HBOT treatment after their second evaluation and had a third neurological evaluation after the cross, when they have completed their HBOT.

The following HBOT treatment protocol was practice: The patient were treated 40 times (each treatment session was given on a separate day) distributed over two months (five days a week). Each session was for 90 minutes in 100% oxygen atmosphere and at pressure of 2 ATA.

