**Randomization**

Since the diversity of the patients included in the study, after signing the informed consent was expected to be high, no stratifies criteria was used. Patients were randomized in 1:1 fashion to either treatment or controlled-cross group.

There is no placebo in the cross group during the control period. The only way to give “placebo” of HBOT, is to bring the patients to the hyperbaric chamber and to increase the environmental pressure- in a way the patients will “feel the hyperbaric pressure” in their ears. However, Henry’s law states: “the amount of a given gas dissolved in a given type and volume of liquid is directly proportional to the pressure of that gas in equilibrium with that liquid”. Thus, hyperbaric environment significantly increases the dissolved oxygen pressure even if a person holding his breath[^76^](#_ENREF_76). Moreover, the alternative of hosting the patients in the hyperbaric chamber without any pressure increase cannot serve as a real placebo since the patients will not feel the pressure. Accordingly, the only real “placebo” could be archived by increasing the pressure and reducing the percentages of the oxygen but that holds significant safety consideration.

From the ethical point of view, it was deemed unethical to “treat” the patients (40 sessions in the hyperbaric chamber) while they actually know that it is a placebo. In order to somewhat compensate for this limitation, the control was a cross group and after the 2^nd^ evaluation at the end of a control period they were crossed to HBOT. The cross for treatment enables intra-group efficacy evaluation in both treatment and control group.

Since the patients knew they were not receiving HBOT during the control period they were not blinded with regard to the treatment arm. Accordingly the ADL and quality of life evaluations were not blinded. Moreover, in the current clinical setting, it was not possible to assure that the NIHSS evaluation could be done completely blinded by the physician. The complete blindness evaluation could be assured in the brain SPECT evaluation done by the radiologist. The correlation between metabolic blinded evaluation of the brain (SPECT) and the neurological un-blinded evaluations give further support and strength to the clinical findings.

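### The protocol's two SPECT descriptions conflict: the three-evaluation schedule implies an untreated control-period scan pair in the cross group, but the SPECT section neither schedules nor grades one

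*Protocol*

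**What the plan says.** The Protocol describes SPECT in four places that bear on this point.

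- **Study protocol.** The evaluations of all patients include "quality of life and brain functional imaging (rCBF-SPECT scan" alongside the neurological examination and activities of daily living. The treated group is evaluated twice. For the cross group the text reads: "The patients of the cross group were evaluated three times – at baseline, after a 2 month control period of no treatment", with a third evaluation after HBOT.
- **Brain functional Imaging SPECT imaging and Analysis.** The schedule sentence is "Single photon emission computed tomography (SPECT) will be conducted before and after HBOT". For the reading, "pre and post treatment studies are fused and normalized to pre-treatment whole brain activity". Two physicians grade each comparison as "1=no change, 2=mild change and 3=significant change", and "Scan visual interpretation will be carried out while blinded to any laboratory or clinical data".
- **Randomization.** ADL and quality of life are acknowledged to be unblinded, and NIHSS blinding could not be guaranteed. For SPECT, "The complete blindness evaluation could be assured in the brain SPECT evaluation done by the radiologist". The section then argues that agreement between the blinded SPECT reading and the unblinded clinical measures strengthens the clinical findings.
- **Objectives, against the statistical sections.** The Objectives list SPECT as a primary endpoint with NIHSS and ADL. Primary Efficacy Analysis Set and Primary Efficacy Analysis name NIHSS and ADL alone as co-primaries.

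**The concern.** The trial is open-label, with an untreated control period in place of a sham. SPECT is the one measure for which the Protocol claims full blinding, and it is used to support the unblinded ones. That support depends on having scan pairs that do not span HBOT, graded the same way by readers who cannot tell which pairs those are. Without such pairs, scan-to-scan variation and reader expectation cannot be separated from an effect of HBOT.

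The schedule matters more than the analysis detail here. A control-period scan that was not taken before the patient crossed to HBOT cannot be recovered later, whatever a statistical analysis plan says.

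**Working it through.** The Protocol gives no SPECT figure to reproduce. The check sets the sections side by side and counts scan pairs.

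**1. Schedule.** Study protocol, read plainly, gives a cross patient SPECT at baseline, month 2 and month 4. The SPECT section names scans before and after HBOT and mentions none across the control period. The NIHSS subsection shows how the Protocol writes a three-visit plan when it spells one out: baseline and two months for everyone, plus a third evaluation in the cross group. The SPECT section has no equivalent sentence and refers to the follow-up study in the singular.

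**2. Pair count.** Let n be the number of patients per arm (1:1 allocation, Randomization section), and assume that everyone completes.

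| | HBOT pairs, treated arm | HBOT pairs, cross arm | Control pairs, cross arm |
|---|---|---|---|
| SPECT section taken literally | n | n | 0 |
| Study protocol schedule | n | n (month 2 to month 4) | n (baseline to month 2) |

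The totals are 2n HBOT pairs and 0 control pairs, against 2n and n. Under the three-evaluation schedule, the untreated share is n / (2n + n) = one third.

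For scale, Sample Size Considerations gives N = 31, for NIHSS and ADL only, without saying whether that is a total or per arm. If it is a total, n = 31 / 2 = 15.5, or about 15 to 16 control pairs. If it is per arm, there are 31. Under the SPECT section taken literally, the number is 0 either way.

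**3. Reading rule if all three scans are taken.** The rule fuses a pre- with a post-treatment study and normalises to pre-treatment activity. A baseline to month-2 pair in the cross group has no post-treatment member, so the rule as worded does not reach it. A cross patient also has two pre-treatment scans, baseline and month 2, and the rule does not say which is the reference. The choice matters: month 2 to month 4 covers HBOT alone, while baseline to month 4 covers the control period plus HBOT.

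**4. Blinding.** Readers are blinded to laboratory and clinical data. Arm, period and scan order are not mentioned. If all graded pairs are pre- versus post-treatment, exposure is the same for every pair by construction, and withholding clinical data cannot conceal it. Grades 2 and 3 both describe improvement and there is no grade for worsening, so random variation can register only as no change or as benefit. Untreated pairs graded in the same session would show how often that happens.

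**The case against.** The case for reading the Protocol more kindly has real weight.

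- **The SPECT sentence does not exclude a control-period scan.** For a cross patient, baseline and month 2 are both before HBOT, so three scans are compatible with it. With the explicit three-evaluation schedule alongside, loose wording is a fair explanation. This stands. A reader might infer that the trial has no untreated SPECT pair, but the documents support that only if the SPECT section governs.
- **Nothing says what the readers are told.** Arm and period could be counted as clinical data, and the Randomization section states the intention of full blinding. This stands too. That readers are aware of exposure is an inference, and under the three-evaluation schedule with all pairs graded it would not follow from the design.
- **The three grades do not mention HBOT.** They rest on perfusion defects and global perfusion, so they could be applied unchanged to a control pair. This is correct for the scale. It does not repair the pairing and normalisation rule, which is tied to treatment.
- **SPECT carries no success criterion.** The co-primaries, sample size and success rule concern NIHSS and ADL, and the listed decision steps contain no between-arm test even for those. A reader might conclude that this point removes the trial's randomised primary comparison, but the documents do not support that. SPECT's role in the argument is supportive, although the Objectives call it primary.
- **Coding of image files is often left to an imaging manual.** That is accepted for the mechanics. Which scans are taken and which pairs are graded belong in the protocol, and there the text conflicts with itself.

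**Conclusion.** The conflict between Study protocol and the SPECT section is real and should be resolved. Its consequence is conditional. If the SPECT section governs, there are 0 graded control pairs instead of n, every graded pair spans HBOT, and the claimed complete blinding does not extend to treated versus untreated. If the three-evaluation schedule governs, the scans exist, but the reading rule leaves out the control pair and does not fix the reference scan for cross patients.

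The counts assume 1:1 allocation and full completion. The size of any bias from scan variation or reader expectation cannot be derived from the Protocol, so no figure is put on it. The point affects the weight that SPECT can bear in support of NIHSS and ADL. It does not change the stated success rule.

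**What to change.** Reconcile the two sections on when SPECT is done. With the scans of the three-evaluation schedule:

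1. State in the SPECT section that scans are taken at baseline and month 2 in both arms and at month 4 in the cross group.
2. Grade the baseline to month-2 pair in both arms by the existing three-grade rule, normalised to the earlier scan of the pair. For the post-cross pair, state which scan is the reference; the same rule applied to month 2 and month 4 makes it month 2.
3. Present all pairs as coded, intermixed single pairs to the same two readers, blinded to arm and period as well as to laboratory and clinical data.
4. Report the month-2 comparison of treated with control patients, and align the status of SPECT between the Objectives and the statistical sections.

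The cost is protocol wording, coding of image files and about n extra pair readings. This assumes that the three-evaluation schedule was intended. If the two-scan plan was intended, covering the control period would add one scan per cross patient (3 − 2 = 1, so n in all), and that has to be weighed when the sections are reconciled. If the control pair is not kept, the Randomization section should no longer present SPECT as a fully blinded support for the clinical endpoints.

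### The SPECT scale has no grade for worsening, masking of scan order is not specified, and the global criterion for the top grade is not measurable as written, so before/after SPECT results lean towards improvement

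*Protocol*

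**What the plan says.** Protocol, Brain functional Imaging SPECT imaging and Analysis, fixes the reading as follows.

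- Scale: the two nuclear medicine physicians compare the scans independently and "grad them as either: 1=no change, 2=mild change and 3=significant change".
- Grade 1: "no change is assign when no visual difference is noted in the number or size of perfusion deficits".
- Grade 2: "mild change is given when a reduced number of perfusion defects are noted or the size of the perfusion defects is reduced".
- Grade 3: "Significant change should be attributed when a global perfusion increment is observe in addition to diminution of defect numbers or size".
- Image preparation: "pre and post treatment studies are fused and normalized to pre-treatment whole brain activity".
- Masking: "Scan visual interpretation will be carried out while blinded to any laboratory or clinical data".
- Tracer: "An injection of 925-1110 MBq (25-30 mCi" and so on, with no correction for injected activity described.

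Scanning is scheduled before and after HBOT, and disagreements are settled by joint review of the images.

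Three other places set the weight of this reading. Protocol, Objectives, lists SPECT among the primary endpoints. Protocol, Randomization, concedes that ADL and quality of life are unblinded and that a fully blinded NIHSS could not be assured. It then says: "The complete blindness evaluation could be assured in the brain SPECT evaluation done by the radiologist". It uses agreement with SPECT to strengthen the clinical findings, and it says the crossover permits efficacy evaluation within each group. By contrast, Protocol, Primary Efficacy Analysis Set and Primary Efficacy Analysis, name only NIHSS and ADL as co-primary.

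**The concern.** SPECT is the one outcome that the Protocol offers as protection against observer bias. A reading that can move only towards benefit cannot give that protection. If apparent deterioration is impossible to record, ordinary reading variation does not average out. It accumulates on the favourable side and appears as an improvement rate even when nothing has changed.

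Two features add to this. A reader who knows which scan came first can resolve doubtful differences in the expected direction. The step from grade 2 to grade 3 depends on a global increase that the stated image processing may erase or may confuse with a difference in tracer activity. At stake is whether an observed SPECT improvement rate can be read as evidence of an effect, and so whether it can support the unblinded NIHSS and ADL results.

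**Working it through.** The Protocol gives no sample size, power or success rule for SPECT, so there is no planned figure to reproduce. N = 31 in Sample Size Considerations concerns NIHSS and ADL, and nothing below depends on it.

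**1. Direction of change against available grade** (inputs: the three grade definitions)

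| Appearance of the second scan | Grade available |
|---|---|
| No difference in defects | 1 |
| Fewer or smaller defects | 2 |
| Fewer or smaller defects plus a global rise | 3 |
| More or larger defects | none |
| Global rise without defect reduction | none that fits |

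Every grade above 1 is an improvement, and the lowest possible score is no change.

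**2. Effect of reading noise when nothing has changed.** Let q be the probability that a pair looks better by chance, and assume the same q for looking worse. The Protocol does not give q, so a range is used. Pairs that look worse are assumed to be entered as grade 1.

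- Reported improvement rate = q. Reported worsening rate = 0.
- Lowest mean grade, with all apparent improvements at grade 2 = 1 × (1 − q) + 2 × q = 1 + q.
- Net change on a scale with matching worsening grades = q − q = 0.

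| Assumed q | Improved, this scale | Worse, this scale | Mean grade, at least | Net change, symmetric scale |
|---|---|---|---|---|
| 0.10 | 10% | 0% | 1.10 | 0 |
| 0.20 | 20% | 0% | 1.20 | 0 |
| 0.30 | 30% | 0% | 1.30 | 0 |

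**3. Between-arm comparison.** If readers do not know the arm and q is the same in both arms, the null difference is q − q = 0, so the one-way scale alone creates no false difference. What is lost is information on harm. As an assumed example, suppose one arm has 40% better and 30% worse, and the other has 15% better and 5% worse. The net change is 40 − 30 = 10 points and 15 − 5 = 10 points, which is equal. The scale reports only 40% against 15%.

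**4. Can grade 3 show a global rise?** The normalisation sentence can be read in two ways.

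- *Totals equalised.* Take four illustrative regions at 100, 100, 100 and 60, with mean 90. A uniform rise of 20% gives 120, 120, 120 and 72, with mean 108. Multiplying by 90/108 returns 100, 100, 100 and 60. The ratio of post to pre is 1.00, so the rise is invisible. The same holds for a 10% rise.
- *Post scan not rescaled to its own total.* Counts then follow injected activity. The permitted range allows 1110/925 = 1.20, an apparent global change of up to 20% with no change in perfusion.

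Under either reading, the text does not define a valid measurement of a global increase.

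**5. Masking.** The stated masking covers laboratory and clinical data. Nothing provides for hiding scan order. Grades worded as a reduction cannot be assigned unless the reader, or a later decoding step, knows which scan came first. No decoding step is described.

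**The case against.** The strongest reply has five parts.

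- *Scan order.* The Protocol never says that readers are shown which scan is pre-treatment, and normalising to the pre-treatment scan is a processing step. This stands. A reader might infer that order is openly displayed, but the documents support only that order masking is unspecified and that the grades presuppose order.
- *Complete blindness.* In context, the claim in Randomization contrasts SPECT with patients and physicians who know the treatment arm. Knowing scan order does not reveal the arm, because cross-group patients also have baseline and two-month evaluations. A reader might infer a flat contradiction between the two sections. The text does not establish one, although it does not provide for masking of order, arm or period by name.
- *Bias towards benefit.* In a randomised comparison masked to arm with equal noise, the shift cancels under the null. This stands and limits the claim. The within-group concern remains, because before/after scanning and intra-group evaluation are uses that the Protocol itself describes.
- *Size.* The noise rate is assumed, and two independent readers with joint resolution may lower it. The ratio of 1.20 is a worst case, with one scan at each end of the range and no activity correction. An imaging manual might contain such a correction, but the Protocol mentions none. These points affect the amount, not the direction.
- *Reach.* The formal hypotheses and sample size concern NIHSS and ADL only. NIHSS, ADL and adverse events can record deterioration, so what cannot be seen is worsening on SPECT alone.

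**Conclusion.** The point holds in this form. The SPECT scale, as fixed in the Protocol, cannot record worsening. Masking of scan order is not specified. The global criterion for grade 3 is not validly measurable under the stated normalisation.

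For before/after and within-group results, symmetric noise q with no true change is reported as an improvement rate of q with no worsening: 10% to 30% for assumed q of 0.10 to 0.30. This rests on equal chance of looking better or worse and on worse-looking pairs being entered as grade 1. For a month-2 comparison masked to arm, with equal noise in the arms, there is no false difference from this source, and the loss is that SPECT worsening goes undetected.

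A reader might infer that the trial's primary conclusion is biased as a whole. The documents do not support that. Objectives lists SPECT as primary, but the co-primary endpoints, hypotheses and sample size are confined to NIHSS and ADL. The weakness falls on SPECT and on its use as blinded support for the clinical results. The two statements of its status must be reconciled.

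**What to change.** Amend the Protocol's SPECT section.

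1. Add worsening grades that mirror the improvement grades, with the same wording in the opposite direction.
2. Present each pair in random order with time point, arm and period masked. Include the cross group's control-period pair. Decode direction only after the readings are locked.
3. Normalise each scan to its own whole-brain or reference-region count, and grade on defect number and size only.
4. Base the SPECT conclusion on the comparison between arms at month 2, and treat within-group results as descriptive.
5. State in one place whether SPECT is primary, and make Objectives agree with the two primary efficacy sections.

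Cost: a protocol amendment rather than only a change to a reading manual, reprocessing of images without the pre-treatment reference, and scrambling of scan labels before reading. The same readers and scans suffice, given that Study protocol includes functional imaging in the evaluations and gives the cross group an evaluation at the end of the control period. The scientific price is that global change is no longer graded.

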**Objectives**

The aim of the current study is to evaluate, for the first time in a prospective randomized study, the effect of hyperbaric oxygen therapy (HBOT) on patients with **chronic** neurological deficiency due to stroke.

- The primary endpoints of the study are to evaluate the effects of the HBOT on:
- National Institutes of Health Stroke Scale (NIHSS)
- Activities of daily living (ADL)
- Brain metabolism as visualized by SPECT
- The secondary endpoints included quality of life evaluation.

The safety of the HBOT in this post stroke population will also be evaluated and any adverse event will be recorded.

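### The SPECT scale has no grade for worsening and counts mixed changes as improvement, so reader noise in before-after results can register only as no change or benefit

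*Protocol*

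**What the plan says.** In the Protocol, section Brain functional Imaging SPECT imaging and Analysis, two nuclear medicine physicians compare the paired scans and "grad them as either: 1=no change, 2=mild change and 3=significant change". The three definitions are:

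- Grade 1: "no change is assign when no visual difference is noted in the number or size of perfusion deficits".
- Grade 2: "mild change is given when a reduced number of perfusion defects are noted or the size of the perfusion defects is reduced".
- Grade 3: "Significant change should be attributed when a global perfusion increment is observe in addition to diminution of defect numbers or size".

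On masking the section states: "Scan visual interpretation will be carried out while blinded to any laboratory or clinical data". On disagreement it states: "Differences in evaluation will be resolve after reviewing the images together".

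The Objectives list "Brain metabolism as visualized by SPECT" among the primary endpoints. The Randomization section presents SPECT as the one evaluation whose blinding can be assured. It uses the agreement of SPECT with the unblinded scores to support the clinical findings, and it says the crossover permits an efficacy evaluation within each group. In the section Study protocol, SPECT is among the evaluations for all patients, and "The patients of the cross group were evaluated three times": at baseline, after the untreated two months, and after HBOT.

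**The concern.** Two faults in the reading rule act in the same direction.

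First, there is no grade for worsening. A scan with more or larger defects is not grade 1, because a difference is visible. It is not grade 2 or 3 either, because both require a reduction. The rule gives the reader nowhere to put it.

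Second, grades 2 and 3 need only one of two features to fall and say nothing about the other. If two defects merge into one larger defect, the number has fallen and the scan meets grade 2. If one defect shrinks while a new one appears, the scan can be read the same way. Such scans cannot be grade 1, so the only definitions they can satisfy are those of improvement.

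Masking does not help, because the asymmetry lies in the scale itself. Joint review does not help either when both readers apply the rule correctly. At stake is the before-after SPECT result, which the plan treats as its blinded evidence of benefit.

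**Working it through.** **Plan's own figure.** The plan gives no rate, hypothesis or sample size for SPECT, so there is none to reproduce. The sample size of 31 concerns NIHSS and ADL only and is unaffected.

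**What the definitions cover.** Number and size can each fall, stay or rise:

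| Number and size | Grade under the text |
|---|---|
| Neither changes | 1 |
| At least one falls, neither rises | 2, or 3 with a global perfusion rise |
| One falls, the other rises (mixed) | literally 2, or 3 with a global perfusion rise |
| At least one rises, neither falls | none |

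The global perfusion condition only separates grade 3 from grade 2. It does not affect whether a pair counts as improved.

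**Noise-only model (assumption; the documents give no reader error rate).** There is no true change. Number and size are independent. Each is read as down with probability *d* and as up with probability *d*.

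- Graded improved: 1 − (1 − *d*)²
- Of which mixed: 2*d*²
- Down only: (1 − *d*)² − (1 − 2*d*)²
- Up only, with no grade: the same, by symmetry
- Unchanged: (1 − 2*d*)²

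At *d* = 0.2: improved 1 − 0.64 = 0.36; mixed 2 × 0.04 = 0.08; down only 0.64 − 0.36 = 0.28; up only 0.28; unchanged 0.36. Check: 0.36 + 0.28 + 0.36 = 1.

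| *d* | Graded improved | of which mixed | of which down only | Up only, no grade | Unchanged | Mixed share of improved |
|---|---|---|---|---|---|---|
| 0.05 | 9.75% | 0.5% | 9.25% | 9.25% | 81% | 5% |
| 0.1 | 19% | 2% | 17% | 17% | 64% | 11% |
| 0.2 | 36% | 8% | 28% | 28% | 36% | 22% |
| 0.3 | 51% | 18% | 33% | 33% | 16% | 35% |

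**What each repair does, at *d* = 0.1 / 0.2 / 0.3.**

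- Mixed scans no longer improved, still no worsening grade: 17 / 28 / 33% of pairs are still graded improved, with nothing to set against them.
- Worsening grade added, mixed scans still improved: improved minus worsened is 19 − 17 = 2, 36 − 28 = 8 and 51 − 33 = 18 points.
- Both repairs, with mixed scans neutral: 17 − 17 = 28 − 28 = 33 − 33 = 0.

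Only the two together remove the bias.

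**Between groups.** If treated and control pairs at two months are graded by the same rule with the same noise, the expected share graded improved is equal in both groups and its difference is 0.

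**The case against.** The strongest reply is that the trial has a control period. Study protocol includes SPECT in every patient's evaluations, so the cross group should have an untreated pair graded by the same rule, and equal noise then cancels in expectation. This stands. A reader might infer that the rule biases the randomised comparison towards HBOT; the documents do not support that if control-period scans are graded identically. Two limits remain. The SPECT section describes scans before and after HBOT and does not itself mention the control period. Real deterioration also goes unrecorded in either group.

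A reader might also blame the either-or wording for the whole effect. That is not supported: mixed scans are 11 / 22 / 35% of the noise-driven improvement at *d* = 0.1 / 0.2 / 0.3, and the larger part is one-directional noise with no worsening grade to offset it. Nor is 2*d*² the net bias of the present plan, since it presupposes a worsening grade that the plan lacks. If number and size always moved in opposite directions, mixed scans could reach 2*d*, or 20 to 60% of pairs, but nothing in the documents supports that pattern.

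Three further points have some weight. The sections Primary Efficacy Analysis Set and Primary Efficacy Analysis name only NIHSS and ADL as co-primary, so no stated success criterion depends on SPECT. Two independent readers with joint resolution may make noise smaller than the upper rows of the table assume. The plural wording on size could be taken to mean the defects overall, in which case a shrinking defect beside a new one need not qualify. That last reading does not rescue the case of merged defects, where the number has plainly fallen.

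**Conclusion.** The point holds for the before-after (intra-group) SPECT results. As written, the scale cannot record a worse scan, and it literally credits a mixed scan as improved, so noise can register only as no change or benefit. In the noise-only model 19 / 36 / 51% of pairs would be graded improved at *d* = 0.1 / 0.2 / 0.3, of which 2 / 8 / 18 points are mixed scans.

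These sizes rest on assumed error rates, symmetric noise and independence of number and size. The upper end is severe, since *d* = 0.3 means a spurious change in each feature in 60% of pairs; at *d* = 0.05 the figure is 9.75%. The direction follows from the definitions and does not depend on the value of *d*. Because the protocol itself states the reading rule, this is a rule to correct and not a detail left to the analysis plan.

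**What to change.** Amend the grade definitions in the SPECT section:

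1. For grade 2, and for the defect part of grade 3, require that defect number or size is reduced, that neither has increased, and that no new defect is seen.
2. Add a mirror-image worsening grade: more or larger defects, with neither feature reduced.
3. Add a neutral category, *mixed / no net change*, for any other visible difference, including one feature down with the other up, or a reduction alongside a new defect. State that it does not count as improvement.
4. Amend grade 1 to match, so that it means no visible difference in number or size and no new defect, and every scan pair falls in exactly one category.

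The cost is wording only, with no extra scan or reader. The small downside is that fewer pairs will be graded improved and the readers apply a slightly longer rule.
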